## Methods

RCTs are the gold standard for evaluating intervention effectiveness by assessing participant outcomes [21]. However, there is growing recognition that a broader mixed methods paradigmatic framework for evaluation research is warranted to generate patient-informed evidence that consider the complex perspectives and experiences of intervention participants and, therefore, are valuable for practice and policy development. In keeping with this innovative approach to evaluation research, the Hans Kai trial will follow a prospective mixed methods intervention design involving an RCT and an interpretative description study. The mixed methods intervention design is an approach to research in which the collection, analysis, and integration of both quantitative and qualitative data are embedded within an experimental quantitative research design [22]. The objective of gathering qualitative data within an experiment, along with the quantitative data on the outcome measures, is to gain an understanding of the personal, contextual experiences of the study participants.

In this mixed methods intervention study, quantitative data on the outcomes of interest will be collected along with qualitative data on the experiences of program participants and facilitators, and integrated within an intervention trial (i.e., RCT) to address the research objectives (see next section for details). The primary research design will be a 6-month RCT that will follow a 2-group parallel superiority design, with a 12–18-month observational follow-up including the intervention participants as well as participants who after completing the 6-month control period decide to participate in the intervention. The RCT and observational follow-up study will involve the collection, analysis, and interpretation of quantitative data (self-reports and objective indicators) on primary, secondary, and tertiary outcomes that will be gathered to evaluate the effectiveness of the Hans Kai program, relative to usual care, in promoting the health and wellbeing of Canadian adults with or without chronic conditions. The 12–18-month observational follow-up study will provide evidence on the long-term durability of any health changes observed during the 6-month RCT period.

To enrich the RCT results, the secondary qualitative strand of the study will be added during and after the intervention by embedding a combination of convergent and explanatory sequential designs into the RCT.

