### Randomized controlled trial

#### Study design

The experimental component of the mixed methods RCT will follow a 6-month 2-group parallel superiority design, with a 12–18-month observational follow-up (see Fig. 2 for details). There will be a 2:1 allocation of participants to the intervention versus the control group. The control group will consist of 6 months of standard care that adults can access in the Canadian Province of Manitoba, including any services and programs that are offered at NorWest, except Hans Kai. At the end of the 6-month control period, the control group participants will be offered the opportunity to join Hans Kai and, once in the intervention, they will be followed for up to 18 months. The participants in the intervention group will be followed for a minimum of 6 months (RCT period) and up to 18 months; however, the randomized controlled portion of the study will last for the first 6 months, while the observational follow-up for them will last 12 months. After baseline, there will be a 2-month period of Hans Kai program implementation during which program participants will attend the Hans Kai Health School, prior to starting regular group meetings.

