#### Study setting

The study will be conducted primarily at NorWest, which is a multidisciplinary health clinic located in the city of Winnipeg (Manitoba, Canada) that engages the community in a variety of co-operative health-based initiatives. NorWest delivers community-based services and programs including primary healthcare, community development, counselling, support services, early learning, and childcare. Eligible individuals throughout Winnipeg can access services in the areas of family violence, immigrant and refugee services, substance abuse during pregnancy, nursing foot care, and Indigenous health. Hans Kai is an ongoing program offered at NorWest. Additional sites in the city of Winnipeg, including any Winnipeg Regional Health Authority (WRHA) site, will also be added as needed to reach the desired sample size of 105 participants (see next section for details). Based on a previous evaluation of Hans Kai [18], it is expected that approximately 85% of the trial participants (*n* = 90) will attend the Hans Kai program and complete the assessment visits at NorWest (15% dropout rate).

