#### Sample size

The primary analysis will be performed based on the pre- to post-intervention changes in the primary outcome, the Mental Health Continuum Short Form (MHC-SF) [23], comparing the mean change scores between the intervention and control participants, with a nested design to account for participant group membership in Hans Kai [24]. Based on data from previous studies [4, 24] and the RCT study design, we expect the changes from baseline MHC-SF scores within each subject group to be approximately normally distributed with a standard deviation of 5. The average within-group pre-post changes in MHC-SF scores in the Hans Kai prospective cohort study were + 6.5 in 34 participants at 6 months [18]. With a planned sample size that accounts for dropouts of 90 adults, with 60 intervention participants and 30 control participants, we would have a power of 80% to detect a true difference in the mean response of intervention and control participants of − 3.1 or 3.1 at the end of the 6-month RCT component [25]. This scenario assumes that the outcomes of each participant will be independent of the Hans Kai peer group they join. However, since part of the Hans Kai program includes forming groups, a very conservative power calculation considers the “effective” sample size for the Hans Kai program to be equal to the number of groups rather than the number of participants. We anticipate that 60 intervention participants will form 10 independent groups of six participants per group. In this very conservative scenario, with 10 groups in the intervention arm and 30 control participants, we would be able to detect a true difference in the mean scores of intervention and control participants of − 5.2 or 5.2 with 80% power. We believe that the actual study power will fall somewhere between the two scenarios presented here. With a starting sample size of 105 adults and an estimated 15% dropout rate during the study period [18], we expect to generate a minimum sample of approximately 90 participants at the 18-month follow-up.

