#### Intervention

In this trial, there will be two groups, an intervention group (*n* = 70) that will immediately enrol in the Hans Kai program and a control group (*n* = 35) that will access standard care available in the Canadian Province of Manitoba, including any services and programs offered at NorWest, except Hans Kai. There will be no special criteria for discontinuing or modifying allocated interventions, except in cases involving worsening of pre-existing health conditions that may either put participants at risk if they continue the program or hinder their participation in the program. The program that will be the intervention in this trial is the Hans Kai program offered at NorWest, with the only modifications being the trial assessment visits described below. The minimum level of compliance to the intervention is 80%; to remain in the trial, study participants must attend a minimum of six health school sessions.

Participants in the control group will remain as close to a “typical” community member as possible as they will be able to receive any other health programming normally available to them in Winnipeg, except the Hans Kai program. Standard of care will be made available to all members of the control group in compliance with the healthcare rights of Canadians and Manitobans holding a Manitoba health card. NorWest staff will provide support to the community members without a Manitoba health cards in obtaining one. The only deviation from standard care in the control group will be the baseline, 3-month, and 6-month visits described below during which the control participants will complete questionnaires and undergo physical assessments.

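### The minimum of about 90 participants at 18 months counts every retained control, although controls enter the long-term follow-up only if they choose to join Hans Kai; at 15% dropout about 90 is the upper end of a range of about 60 to 90

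*Protocol article*

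**What the plan says.** All references are to the protocol article.

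- **Sample size.** The long-term number is introduced with "With a starting sample size of 105 adults and an estimated 15% dropout rate during the study period", and the sentence concludes that "we expect to generate a minimum sample of approximately 90 participants at the 18-month follow-up". The same section uses 90 adults (60 intervention, 30 control) for power at 6 months.
- **Study design.** "There will be a 2:1 allocation of participants to the intervention versus the control group"; the Intervention section gives the arm sizes as 70 and 35. Once the 6 months of standard care are over, "the control group participants will be offered the opportunity to join Hans Kai", and those who do so are then followed in the program.
- **Methods, introduction.** The observational follow-up consists of the intervention participants and "participants who after completing the 6-month control period decide to participate in the intervention".
- **The follow-up observational study.** For people coming from the control arm, follow-up is described only as the health school followed by program visits.
- **Study setting.** About 85% of trial participants, given as n = 90, "will attend the Hans Kai program and complete the assessment visits at NorWest".

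The article states no uptake rate for the offer and describes no assessments after month 6 for controls who decline it.

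**The concern.** A minimum should hold across the outcomes that the design allows. The stated one holds only if practically every retained control accepts an optional offer. The number and the entry rule for the follow-up therefore do not fit together.

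The observational follow-up is the trial's stated source of evidence on how long any 6-month changes last, and the Statistical analysis section plans a secondary analysis over 0 to 20 months. A reader who takes 90 as a floor will expect more people behind those results than the design secures. Such a reader may also not notice that up to a third of them are controls who opted in after 6 months of standard care.

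**Working it through.** **Inputs.** 105 randomised and 15% dropout (Sample size); 70 intervention and 35 control (Intervention); follow-up entry limited to intervention participants plus controls who opt in (Methods introduction, Study design). Uptake u, the share of retained controls who join Hans Kai, is not in the document. It is an assumption here and is varied from 0 to 1.

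**Step 1: reproduce the stated figure.**

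- Total: 105 × 0.85 = 89.25, which matches approximately 90.
- By arm: 70 × 0.85 = 59.5 intervention and 35 × 0.85 = 29.75 control.

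The multiplication is correct. It reaches 90 only because all 29.75 retained controls are counted, that is, u = 1.

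**Step 2: apply the protocol's entry rule.** Expected number at the long-term follow-up = 59.5 + 29.75 × u.

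| Uptake u (assumed) | Control-origin | Total |
|---|---|---|
| 0% | 0 | 59.5 |
| 25% | 7.4 | 66.9 |
| 50% | 14.9 | 74.4 |
| 75% | 22.3 | 81.8 |
| 90% | 26.8 | 86.3 |
| 100% | 29.75 | 89.25 |

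**Step 3: does the word approximately rescue the figure?** Being within 3% of 90 means at least 87.3. This needs u ≥ (87.3 − 59.5) / 29.75 = 0.93. So about 93% of retained controls must join.

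**Step 4: when could 90 be exceeded?** With dropout d, the total is (1 − d) × (70 + 35u). It exceeds 90 when d < 1 − 90 / (70 + 35u).

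- u = 100%: d below 1 − 90/105 = 14.3%
- u = 90%: d below 1 − 90/101.5 = 11.3%
- u = 75%: d below 1 − 90/96.25 = 6.5%
- u = 50%: never, because even with no dropout the total is 87.5

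**Step 5: the 6-month comparison.** Its 60 + 30 is 59.5 and 29.75 rounded. It depends on retention to month 6 and not on controls joining the program, so it stands.

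**The case against.** **The multiplication is right and the follow-up is openly called observational.** Both are true. The fault is an unstated assumption of near-complete uptake behind the word minimum. The document also does not hide that control-origin participants select themselves, and it claims no power or precision at 18 months.

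**Uptake may well be high.** Entrants must report motivation to change their lifestyle and be willing to comply with trial requirements, and the Study design section says that both groups complete two follow-up visits. This makes the low-uptake rows of the table less likely, and the figure of 60 should be read as the zero-uptake extreme and not as a forecast. It does not make 90 a minimum: even at 90% uptake the total is about 86. The sentence on both groups makes no provision for decliners, while the Methods introduction defines who is in the follow-up.

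**The 15% might already include controls who decline.** The Sample size section calls it dropout and takes it from the earlier evaluation of Hans Kai. The Background describes that study as pre-post surveys and interviews of program participants, which would not measure uptake after a control period.

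Three stronger readings are tempting, and the documents do not support them.

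- A reader might infer that 90 is an absolute ceiling. It is the upper end only at 15% dropout; Step 4 shows how lower dropout with high uptake could exceed it.
- A reader might infer, from the use of 90 at both 6 and 18 months, that the plan allows for no loss in between. The Sample size section speaks of "an estimated 15% dropout rate during the study period". This can be read as cumulative loss to 18 months, in which case 60 + 30 is a cautious figure at 6 months.
- A reader might conclude that the long-term analysis must rest on the intervention-origin participants, with the control-origin participants as support. That is a choice of analysis which an analysis plan may settle; it is not the correction of an error in this document.

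**Conclusion.** The point holds as an inconsistency between the stated long-term sample size and the stated entry rule for the follow-up. At the assumed 15% dropout, the design delivers about 60 intervention-origin participants plus between 0 and about 30 control-origin participants. The stated minimum of about 90 is the top of that range, and at zero uptake the number is one third lower ((90 − 60) / 90).

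This rests on two things: that the 15% applies equally to both arms, as the protocol's own 60 + 30 split implies, and that controls who decline are not followed, since no section provides for it. The n = 90 in the Study setting section needs the same correction, because it too has every retained control attending the program. The consequence is limited to the description of the observational follow-up and the secondary long-term analysis.

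**What to change.** - In Sample size, keep 90 (60 + 30) as the expected sample for the 6-month comparison. Replace the 18-month sentence with: about 60 intervention-origin participants, plus up to about 30 control-origin participants depending on how many join Hans Kai, at 15% dropout.
- In Study setting, restate in the same terms the n = 90 expected to attend Hans Kai.
- With the long-term results, report how many controls took up the offer and how many participants come from each origin arm.

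This costs a few lines of wording and two counts in the report. Randomisation, sample size and primary analysis do not change. The drawback is that the stated follow-up size becomes less favourable.

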#### Randomization

Following the eligibility screening and the baseline assessment visit, participants will be randomly allocated to either the intervention group or the control group using a computer-generated random sequence. After screening and enrollment, once participants are determined to be eligible to participate in the clinical trial, a research team member will press a randomize function within the REDCap secure system. Participants will be assigned with a 2:1 ratio of intervention to control groups. To ensure allocation concealment and minimize bias, randomization will be performed by a third-party biostatistician not affiliated with the research team. The randomization sequence will be uploaded into the University of Manitoba Research Electronic Data Capture (REDCap) system randomization module [26, 27].

#### Blinding

Blinding of participants and study staff is not possible given the nature of the intervention, but the study statistician and the entire data management team will be blinded to allocation during analysis, making this a prospective randomized open blinded end-point study [28].

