**Methods:**

This research will involve a mixed methods trial combining an experimental component with a qualitative component. The experimental component will involve a 6-month 2-group parallel superiority randomized controlled trial (RCT) in which 105 participants will be randomly assigned to two conditions, an intervention group (*n* = 70) that will participate in the Hans Kai program and a control group (*n* = 35) that will have access to standard care using a computer-generated random sequence; blinding will not occur. The RCT will test the impact of the program on several health outcomes and will be followed by a 12–18-month observational follow-up study that will provide data on the long-term durability of the 6-month RCT health outcomes. The qualitative component will investigate the experiences of program participants (*n* = 30) and facilitators (*n* = 15) to identify the main strengths and limitations of Hans Kai, uncover potential implementation issues, and elucidate the mechanisms through which the program works. The population of interest will include adults aged 18 + with or without chronic health conditions who self-report an interest in taking control of their own health and improving their lifestyle. In the RCT, all outcomes of interest will be measured using a multi-method approach, involving self-report questionnaires and objective indicators, and within-subject mean changes in outcomes over time between the two groups will be compared to address the RCT aims. Similarly, in the qualitative component, a multi-method approach, involving in-depth individual interviews, photovoice, and online surveys, will be used to reach a deeper and more nuanced understanding of the program strengths, how the program works, and for which people it is more effective. Adaptable components of the program will also be investigated and modified according to the feedback provided by the RCT participants. In the mixed methods integration of evidence, the qualitative findings will be used to explain the quantitative RCT results.

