The standardized self-report questionnaire Pittsburgh Sleep Quality Index (PSQI) [32] will be used to subjectively measure sleep quality, habits, and patterns subjectively. This scale includes nine items that assess seven aspects of sleep: (1) subjective sleep quality, (2) sleep latency, (3) sleep duration, (4) habitual sleep efficiency, (5) sleep disturbances, (6) use of sleeping medications, and (7) daytime dysfunction over the last month. Scoring varies across items; however, an overall score can be calculated by summing the seven component scores, yielding a Global PSQI score ranging from 0 to 45, with higher scores indicating poorer sleep quality (secondary outcome 6). The PSQI has shown acceptable internal homogeneity, consistency (test–retest reliability), and validity. Additionally, a global PSQI score greater than 5 yield a diagnostic sensitivity of 89.6% and specificity of 86.5% (*k* = 0.75, *p* < 0.001) in distinguishing good and poor sleepers.

Sleep quality (Fitbit sleep score) and length (sleep time) will also be measured objectively using data provided by a Fitbits that participants will wear for 7 days at each assessment point [33]. The average of these seven measurements will be used.

Fitbits will also be used to measure behavioral changes in terms of physical activity (secondary outcome 7) [34, 35]. Specifically, at each assessment point, daily step count and moderate-to-vigorous physical activity will be recorded over a 7-day period, and the average of these seven measurements will be used as an indicator of participants’ level of physical activity.

The tertiary objective of this RCT is to investigate the impact of the Hans Kai program on clinical cardiometabolic health indicators, including blood glucose, waist circumference, body weight, and blood pressure. These indicators will be assessed objectively by a registered nurse who every 6 months will perform a clinical exam of study participants.

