#### Procedure

At the baseline assessment, all participants (both the intervention and control group) will undergo a clinical exam that will be performed by a trained research team member, who will measure participants’ blood glucose levels, blood pressure, weight, and waist circumference according to provincial health standard protocols. All clinical measurements will be taken three times, except blood glucose, which will be measured only once using a glucometer that tests capillary blood samples taken by finger prick sampling. Blood pressure will be measured in triplicate following 10 min of acclimatization to the measurement room, with a 2-min break between measurements. The average of the three assessments will be used as measure of blood pressure. Following the clinical assessment, participants will be asked to complete all self-report measures, including a sociodemographic questionnaire, the MHC-SF, the Revised UCLA Loneliness Scale, the PHCS, the Adapted Healthy Eating Assessment, and the PSQI. Fitbits will also be used to objectively assess changes in participants’ physical activity as well as sleep quality and patterns. Participants will be shown by the study staff how to wear the Fitbit and will be given basic instructions on its use. Study participants will be asked to wear the Fitbit for 7 complete days on the assessment week, including when they are asleep so that their sleep quality and patterns can be recorded.

Following the baseline assessment, study participants will be randomly assigned to either the intervention group or the control group (see Fig. 3 for Consort flow diagram) [36]. After random allocation to either trial condition, participants in the intervention group will immediately enter the Hans Kai program, while participants in the control group will be exposed to 6 months of standard care. Participants who are randomized to the control group will receive $100 CAD (made out in two payments of $50 CAD, one at the 3-month visit and one at 6-month visit). This remuneration for participants who are randomly assigned to the control group instead of the intervention group will be used as a strategy to improve adherence to the intervention protocol. We will also monitor adherence by tracking attendance to the health school and trial visits. See Fig. 4 for the SPIRIT flowchart of the schedule of enrollment, intervention, and assessments.

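### Masking is ruled out for all study staff, although the person taking waist and blood pressure at 6 months could be kept unaware of the arm

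*Protocol article*

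**What the plan says.** All references are to the protocol article.

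- **Blinding:** "Blinding of participants and study staff is not possible given the nature of the intervention". The same sentence adds that "the study statistician and the entire data management team will be blinded to allocation during analysis", "making this a prospective randomized open blinded end-point study". The abstract (Methods) says "blinding will not occur".
- **Outcomes:** the tertiary objective covers cardiometabolic indicators, "including blood glucose, waist circumference, body weight, and blood pressure". On who measures them: "These indicators will be assessed objectively by a registered nurse who every 6 months will perform a clinical exam of study participants". Table 1 also gives the clinical exams to a registered nurse, at baseline and then every 6 months.
- **Procedure:** at baseline, participants in both groups "will undergo a clinical exam that will be performed by a trained research team member". Measurements follow provincial standard protocols and are taken three times, except glucose, which is a single finger-prick glucometer reading. Blood pressure is averaged over three readings, after a rest period and with breaks between readings.
- **Order of events:** "Following the baseline assessment, study participants will be randomly assigned to either the intervention group or the control group".
- **Statistical analysis:** the randomised comparison is of mean within-subject changes from baseline to 6 months. Results with p below 0.05 are called significant, with no multiplicity adjustment.

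**The concern.** The intervention is a taught health school followed by peer-led group meetings. Attending or running it reveals the arm, so participants and programme staff cannot be masked. A person who only measures waist, weight, blood pressure and glucose does not have to attend or run anything. The stated reason therefore does not support ruling out masking for every member of staff. Because the article fixes this as a design decision, it is more than a detail left to a fuller document.

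A tape measure leaves room for judgement in placement, tension and reading. A manual blood pressure reading leaves some too. An examiner who knows the arm can lean, without intending to, towards the expected result. Any such lean at 6 months passes unchanged into the between-arm difference in change, and averaging three readings does not remove it. With no multiplicity adjustment, a single spurious cardiometabolic result would be reported as significant.

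**Working it through.** **Which outcomes and visits are exposed**

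| Measurement | Exposed to an examiner who knows the arm? | Reason |
|---|---|---|
| Baseline clinical exam | No | Done before randomisation |
| Waist, after randomisation | Yes | Depends on the observer |
| Blood pressure, after randomisation | Depends on the device | The article does not say whether it is manual or automated |
| Weight, glucometer glucose | Hardly | Largely read from a device |
| MHC-SF (primary) and other questionnaires | No | Self-reported; masking the nurse changes nothing |
| Fitbit measures | No | Recorded by the device |

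The point therefore concerns two tertiary outcomes at the visits after randomisation.

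**Check of the plan's own figure**

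The plan has no figure for assessor bias. Its nearest figure is the power statement in Sample size: 60 v 30, SD 5, difference 3.1, power 80%.

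- SE = 5 × √(1/60 + 1/30) = 5 × 0.2236 = 1.118
- 3.1 / 1.118 = 2.77
- Two-sided 5% test: power 79.2% (normal approximation) or 78.3% (noncentral t, 88 df)

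This is close to the stated 80%, so 60 v 30 is a fair basis for what follows.

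**Illustration with assumed inputs**

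From the document: 60 v 30 completers and the 0.05 level. I assume a two-sided test, an SD of change in systolic pressure of 12 mmHg (range 10 to 15), and an average assessor shift favouring Hans Kai of 2 to 3 mmHg. A shift of 1 mmHg is added to show the lower end. There is no true effect.

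- SE = SD × 0.2236, which is 2.236, 2.683 and 3.354 mmHg for SD 10, 12 and 15
- Noncentrality = shift / SE
- False-positive chance = P(|t| > 1.987) under the noncentral t with 88 df

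| Shift (mmHg) | SD 10 | SD 12 | SD 15 |
|---|---|---|---|
| 0 | 5.0% | 5.0% | 5.0% |
| 1 | 7.3% | 6.6% | 6.0% |
| 2 | 14.3% | 11.4% | 9.1% |
| 3 | 26.4% | 19.8% | 14.3% |

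For waist the same calculation can be read on a standardised scale. With a z-test and 60 v 30, a lean of 0.1, 0.2 or 0.3 SD of change gives a false-positive chance of 7.3%, 14.5% or 26.9%. Which of these is realistic cannot be judged from the document.

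Masking the examiner changes no sample size or power figure.

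**The case against.** **The safeguards already in the plan.** Standard protocols, triplicate readings, a rest period and averaging narrow the examiner's discretion, and baseline is measured before allocation. This stands in part. A fixed procedure limits how large a lean can be, but it does not remove a systematic one.

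**The size is hypothetical.** Neither the SD nor the shift comes from the document, and an automated cuff would make a shift of 2 to 3 mmHg hard to produce. This stands. The table shows how sensitive the comparison is; it does not estimate the bias in this trial.

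**The assessor descriptions.** A reader might infer from the two descriptions that a research team member measures at baseline and a nurse at follow-up, so that a change of assessor distorts the results. The document does not support that. Table 1 already assigns the nurse at baseline, and the nurse may be the trained team member meant in Procedure. Even a real switch would apply to both arms alike and would not bias the randomised comparison. What remains is wording to align.

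**Masking is not as simple as not telling the nurse.** The full exam falls 6 months after the health school in the intervention group but 6 months after enrolment in controls. Only controls are paid at the 6-month visit. Programme and assessments are both expected mainly at one clinic, and nothing says the nurse is free of programme duties. This stands, and it means that masking would be partial.

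**This is a condensed article.** Access rights and examiner assignment can sit in the full protocol. But the article does more than omit them: it states that staff masking is impossible.

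**Conclusion.** The point holds in a limited form. The stated reason does not justify leaving the follow-up examiner unmasked, and as written nothing keeps that person unaware of the arm. Waist circumference and, depending on the device, blood pressure are therefore open to observer bias at 6 months. With 60 v 30 completers and the assumed SD and shift, the false-positive chance for systolic pressure would be about 9 to 26% instead of 5%. It would be nearer 6 to 7% if the shift were only 1 mmHg.

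A reader might go further and infer that observer bias could account for the tertiary results as a whole. That is not supported, because weight and glucose are largely read from a device. Nor does the point touch the primary outcome or the power calculation. This is a worthwhile, low-cost improvement to tertiary outcomes and does not threaten the main conclusion of the trial.

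**What to change.** 1. In Blinding, limit the statement that masking is impossible to participants and the staff who deliver the programme.
2. In Outcomes, Table 1 and Procedure, state that the planned registered nurse does the clinical exams, is not told the arm, has no part in Hans Kai delivery or randomisation, and cannot see the allocation field in REDCap. State that participants are asked not to disclose their arm.
3. Use the same assessor description in Procedure as in Outcomes and Table 1, and bring the abstract's statement on blinding into line.
4. If the nurse cannot be kept apart from the programme, report waist and blood pressure as open-label assessments.

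The cost is protocol wording, a REDCap access setting and some scheduling. No extra staff are needed if the planned nurse has no programme duties, which the article does not say. Masking will remain imperfect, because participants may disclose their arm and visit timing differs between arms.
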